## Abstract

**Background:**

Major depression is a common psychiatric disorder, frequently taking a chronic course. Despite provision of evidence-based treatments, including antidepressant medication and psychological treatments like cognitive behavioral therapy or interpersonal therapy, a substantial amount of patients do not recover. Mindfulness-Based Cognitive Therapy (MBCT) has been found to be effective in reducing relapse in recurrent depression, as well as lowering symptom levels in acute depression. The effectiveness of MBCT for chronic, treatment-resistant depression has only be studied in a few pilot trials. A large randomized controlled trial is necessary to examine the effectiveness of MBCT in reducing depressive symptoms in chronic, treatment-resistant depression.

**Methods/Design:**

A randomized-controlled trial is conducted to compare MBCT with treatment-as-usual (TAU). Patients with chronic, treatment-resistant depression who have received antidepressant medication and cognitive behavioral therapy or interpersonal therapy are included. Assessments take place at baseline and post intervention/TAU-period. The primary outcome are depressive symptoms. Secondary outcomes are: remission rates, quality of life, rumination, mindfulness skills and self-compassion. Patients in the TAU condition are offered to participate in the MBCT after the post TAU-period assessment. From all completers of the MBCT (MBCT condition and patients participating after the TAU-period), follow-up assessments are taken at three and six months after the completion of the MBCT.

**Discussion:**

This trial will result in valuable information about the effectiveness of MBCT in chronic, treatment-resistant depressed patients who previously received antidepressant medication and psychological treatment.

**Trial registration:**

trialregister.nl NTR4843, registered 14^th^ October 2014.

## Background

Major depression is one of the most common psychiatric disorders. It has a large impact on individual’s wellbeing and leads to high societal costs [1, 2]. The duration of a depressive episode is highly variable. Whereas the majority of people in the general population with a major depressive episode recovers within several months, approximately 20 % of all depressed patients develop a chronic course of depression [2, 3]. The latter is associated with higher suicidality [4], increased comorbidity with other psychiatric disorders, and impaired physical and psychosocial functioning [5]. According to DSM-IV criteria, a depressive episode is defined as chronic if the depressive episode persists for at least two years [6]. However, results of a large prospective epidemiological study on the prevalence of major depression in the Dutch population show, that -even if treated in mental health care- the rate of recovery decreases after a few months. After one year, recovery rates virtually stagnate, meaning that if no recovery has taken place within 12 months the probability to develop a chronic course of depression- as defined in the DSM-IV- increases substantially [3].

Not only a chronic course of symptoms but also several unsuccessful therapeutic interventions can be indicative of a severe depressive episode. Patients who do not respond to treatment are often described as ‘treatment-resistant’. However, up till now, an unified and clear definition of ‘treatment-resistant depression’ is lacking. Definitions range from one single unsuccessful attempt at antidepressant medication (ADM) to several pharmacological interventions combined with electro-convulsive therapy [7, 8]. In most clinical studies, a depressive episode is regarded as treatment-resistant when successive treatment with two antidepressants has not led to a significant improvement of depressive symptoms. Interestingly, this definition does not take response to psychological treatment into account, while cognitive behavior therapy (CBT) or interpersonal therapy (IPT) are part of international treatment guidelines for recurrent and chronic depression [9]. Importantly, research has shown that even when psychological and pharmacological treatment options are combined, a substantial amount of patients fails to respond [10, 11]. This means that there is a dire need of new treatment options for chronic, treatment resistant depression.

In recent years, mindfulness based interventions have been developed as a treatment focused on distress caused by long-lasting somatic and psychological disorders [12]. Mindfulness is defined as non-judgmental awareness of the present moment [13] and was introduced by Kabat-Zinn [14] as a treatment option for patients with chronic somatic conditions. Segal, Williams and Teasdale [15] adapted the program for patients with recurrent depression, naming it ‘Mindfulness Based Cognitive Therapy’ (MBCT). MBCT is a group intervention, consisting of eight weekly 2.5 h sessions and a silent day of 6 h. It involves meditation exercises as well as cognitive behavioral techniques. MBCT is designed to address processes that are associated with the onset, maintenance and recurrence of depression, such as maladaptive automatic cognitive and behavioral patterns in reaction to negative emotions or thoughts. In first instance participants are taught to allow and acknowledge negative emotions and thoughts as they are, without having judgments about them or reacting to them. In this way, they start recognizing their own maladaptive automatic patterns. By creating a greater awareness of habitual behavioral and cognitive patterns (e.g. avoidance or rumination) participants learn to deliberately disengage from them. Another important part of MBCT is to develop self-compassion. MBCT differs from CBT in the sense that the focus of cognitive therapy is more on the content of thoughts, while MBCT focuses on the process of thinking.

In chronic depression, maladaptive automatic cognitive and behavioral patterns often have become habitual. Patients often experienced several episodes of depression and an early onset of the disorder. To learn to react in a different way to these maladaptive automatic cognitive and behavioral patterns and to develop a non-judgmental awareness of depressive symptoms might be especially useful for this population. Therefore MBCT might be effective in lowering depressive symptoms in chronic, treatment resistant depression.

A recent meta-analysis [16] shows that MBCT is effective in preventing relapse in patients with recurrent depression. Additionally, there is evidence, that MBCT not only decreases chance of relapse of depression, but that it lowers levels of residual or current depressive symptoms. The first studies investigating the effect of MBCT on residual symptoms in remitted depressed patients found significant improvements of depressive symptoms [17, 18]. More recently, a meta-analysis was conducted on the effects of MBCT in patients currently meeting diagnostic criteria for a major depressive disorder [19]. The authors concluded that MBCT reduces depressive symptoms in currently depressed patients and might be as effective as CBT. One of the studies [20] included in the meta-analysis specifically investigated possible differences of the effectiveness of MBCT between remitted but still symptomatic and currently depressed patients. The results indicate that MBCT was effective for both remitted and currently depressed patients.

First results indicate that MBCT might also be a promising treatment option for chronic depression. Kenny and Williams [21] reported a decrease in depressive symptoms in a sample of currently depressed patients who experienced symptoms for one year or longer, preceded by three or more previous episodes. In line with that, Eisendrath et al. [22] found a significant decrease in depressive symptoms after MBCT in currently depressed patients who previously received at least two different antidepressants before starting the MBCT training. In addition to these non-randomized studies, two randomized-controlled pilot trials demonstrated a significant reduction of depressive symptoms in chronically depressed patients. Barnhofer et al. [23] found that after following MBCT less participants met full criteria for a major depressive episode compared to a control group. Another study [24] investigated the effectiveness of person-based cognitive therapy, a therapy combining mindfulness techniques and cognitive therapy, in chronic depression and found significant improvement of depressive symptoms and mindfulness skills in the therapy group compared to the control group. Importantly, all of these studies report a good acceptance of the MBCT training procedures by chronically depressed patients.

In sum, there is preliminary evidence that MBCT might be effective in reducing depressive symptoms in chronic, treatment-resistant patients. However well-powered randomized controlled trials are necessary to systematically examine the effectiveness of MBCT compared to treatment as usual in this severely affected patient group. With the current ongoing trial we will hopefully contribute to the knowledge about treatment options for patients with persistent depressive symptoms. Taking into account the high risk for chronic depression if symptoms persist for more than one year [3] we will recruit patients experiencing a depressive episode for 12 months or longer who underwent previous pharmacological and psychological treatment.

### Aims

The aim of the current study is to investigate the effect of MBCT compared to treatment as usual (TAU) on depressive symptoms in patients with a current depressive episode persisting for at least 12 months, who previously received pharmacological treatment, as well as either CBT or IPT. We hypothesize that patients who receive MBCT in addition to TAU will report lower levels of depressive symptoms, higher quality of life, and less rumination, compared to TAU alone. In addition, we expect that mindfulness skills and self-compassion will improve in the MBCT condition. Possible effects of level of treatment-resistance and experience of childhood trauma on treatment effect will also be investigated.

## Methods/Design

### Design

This study is a multi-center open-labeled randomized controlled trial with two groups: MBCT+ TAU vs. TAU. The study has been approved by the Medical Ethics Committee Arnhem-Nijmegen (nr. 2012/339) for all participating sites. Before randomization, written informed consent is obtained from all participants. Primary and secondary outcome measures are assessed at baseline and after MBCT + TAU (8–12 weeks) or after a TAU-period (8–12 weeks). Participants allocated to the TAU condition are offered participation in the MBCT after completion of the TAU-period and first follow-up assessment. Of all participants who completed the MBCT, follow-up measures take place at three and six months after the end of treatment. For an overview of the recruitment and measurement points see Fig. 1.

**Fig. 1 Fig1:**
[figure not shown]
Flowchart of the recruitment and measurement points

### Participants

The study population consist of outpatients with a current depressive episode lasting for 12 months or longer who previously received ADM, as well as either CBT or IPT. Patients are recruited at a university medical center (Radboudumc Centre for Mindfulness) and at different locations of a regional mental health institution (Pro Persona) in The Netherlands. Patients can be referred by health care professionals, or can contact the research team themselves for participation. Patients receive an information letter and are contacted by phone one week later by the research team. Patients are informed that participation in the study is completely voluntary and that they can withdraw from the study at any time. Participants are free to receive additional treatment or to change their (dose of) pharmacological medication during the study period.

Inclusion criteria:Age ≥ 18A current diagnosis of major depressive disorder according to DSM-IV criteria with a duration of ≥12 monthsModerate to high level of current depressive symptoms (Inventory of Depressive Symptomatology- Self Report, IDS-SR ≥ 21)At least one adequate trial of ADM during the current episode (defined as: appropriate doses of antidepressant medication for ≥ 4 weeks; or patient’s refusal to use medication in contrast to advise by a psychiatrist)Previous psychological treatment during the current episode (defined as: ≥ 10 sessions of CBT or IPT; or < 10 sessions if discontinued because of patient’s withdrawal)

Exclusion criteria:Current psychotic symptomsBipolar disorder according to DSM-IVCurrent alcohol or drugs dependence according to DSM-IVRecent electro convulsive therapy (<3 months)Current somatic disorder (partly) explaining depressive symptomsPhysical-, language-, cognitive-, or intellectual impairments which interfere with participation in MBCT or assessmentsPrevious MBCT training

### Procedure

**Assessment of eligibility, baseline measures and randomization**

All patients who indicated their interest in the study are invited for a research interview. Written informed consent is obtained during this first appointment. To assess eligibility and to classify comorbid psychiatric disorders, participants are interviewed by a research psychologist or psychiatrists in training with the depression, anxiety, psychosis and addiction modules of the Mini International Neuropsychiatric Interview (MINI; [25]). In addition, the following disorder-related characteristics are assessed: duration of current major depressive episode, number of psychological treatment sessions (i.e. CBT and/or IPT) during current major depressive episode, duration and doses of pharmacological treatments during the current depressive episode, number of depressive episodes during lifetime and age of onset. On the base of these details the research assistant fills out the Dutch Measure for quantification of Treatment Resistant Depression (DM-TRD, [26] [27]). After completion of the baseline questionnaires, a computer program is used to randomly allocate patients to either MBCT + TAU or TAU. A minimization strategy is used for severity of symptoms (IDS-SR ≥21 and ≤31 vs. > 31 and ≤ 39 vs. > 39) and duration of major depressive episode (1–2 years vs. > 2 years). If the period between randomization and start of the MBCT training exceeds four weeks in the MBCT + TAU condition, a repeated baseline assessment takes place.

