### Interventions

**MBCT + TAU**

The MBCT consists of eight weekly sessions of 2.5 h in groups of 8–15 patients and one additional day of silent practice between the 5^th^ and 7^th^ session. Participants are asked to do daily homework assignments. MBCT combines mindfulness meditation techniques, as sitting meditation and the body scan with elements of cognitive therapy such as psycho education and the identification of automatic negative thoughts. The MBCT manual described by Segal, Williams and Teasdale [13] is used. Participants are enrolled in regular MBCT trainings provided at the Radboudumc Centre for Mindfulness and Pro Persona for (remitted) depressed patients. This means that the training groups not only consist of study participants but also of regular patients with a wide range of depressive symptoms.

MBCT trainings are taught by experienced mindfulness trainers who completed a 2-year post-graduate teacher training program at the Radboudumc Centre for Mindfulness. With this, they all meet the training criteria described in the MBCT good practice guidelines (UK Mindfulness-Based Teacher Trainer Network, 2011). Two MBCT sessions of each trainer are videotaped to verify adherence to the MBCT protocol. In addition to MBCT the participants receive TAU.

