### TAU

TAU may consist of any treatment the participant or current mental health care specialist sees as necessary. Participants are encouraged to continue treatment they followed prior to enrolling in the study. The number of treatment sessions and use of antidepressant medication are recorded.

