### Primary analysis

The effect of condition (MBCT + TAU vs. TAU) on the primary outcome measure (depressive symptoms) will be examined using general linear models. Condition and baseline score of depressive symptoms will be included as independent variables, depressive symptoms at FU1 as the dependent variable. Because MBCT is delivered in mixed groups consisting of regular patients and a few study participants and previous studies did not yield an effect of therapy group [20], we will not incorporate a random group effect.

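### Two institutions recruit and run MBCT, but institution is neither a balancing factor nor a model term, which costs some precision and could be remedied for one degree of freedom

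*Protocol article*

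**What the plan says.** The Design section states: "This study is a multi-center open-labeled randomized controlled trial with two groups". Under Participants, recruitment takes place at a university medical center and "at different locations of a regional mental health institution". Both institutions also provide the intervention: "Participants are enrolled in regular MBCT trainings provided at the Radboudumc Centre for Mindfulness and Pro Persona".

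The section on eligibility, baseline measures and randomization names the balancing factors: "A minimization strategy is used for severity of symptoms (IDS-SR ≥21 and ≤31 vs. > 31 and ≤ 39 vs. > 39) and duration" of the depressive episode, the latter in two bands. No other factor is listed.

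The Primary analysis section fixes the model: "Condition and baseline score of depressive symptoms will be included as independent variables", with the IDS-SR at FU1 as the outcome. Secondary analyses carries the same terms over to quality of life, rumination, mindfulness skills and self-compassion; remission is compared by a χ² test. The Primary analysis section gives a reason for leaving out a random effect of therapy group. Nothing is said about institution. The Analyses plan compares the arms on baseline characteristics but attaches no adjustment to that comparison.

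**The concern.** Institution is known before allocation and is an obvious candidate prognostic factor in a multi-centre trial. Here the article does not leave the matter open for a later document: it lists the balancing factors and the model terms, and institution is in neither list.

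Two consequences follow if patients at the two institutions differ in their FU1 score for reasons other than baseline IDS-SR. First, that difference stays in the residual and widens the confidence interval. Second, with 94 patients and no balancing on institution, the arms can differ in institution mix by chance, and the estimate from that particular sample then moves by the imbalance multiplied by the site effect. Adding institution after seeing the data would be open to the charge of choosing the model by its result, which is the reason to settle it in advance.

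**Working it through.** **Inputs from the protocol (Power analysis and sample size).** Effect size d = 0.53, alpha 0.05, power 80%, correlation between baseline and first follow-up 0.5, 43 per condition, 8 drop-outs, 94 in total. Sidedness is not stated.

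**Inputs assumed.** The protocol gives neither the share of patients from each institution nor any site effect. I take a 50:50 split and a residual site effect g of 0.3 to 0.5 SD on FU1, and vary the split below.

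**1. The plan's own figure.** Residual SD after adjustment for baseline = √(1 − 0.5²) = 0.866. Per arm, n = 2 × (1.960 + 0.842)² × 0.75 / 0.53² = 41.9, so 42 by the normal approximation. With the noncentral t distribution and one covariate, power is 79.1% at 42 and 80.1% at 43. The stated 43 is reproduced on a two-sided test (one-sided gives 34), and 2 × 43 + 8 = 94.

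**2. Standard error of the planned estimate.** 0.866 × √(2/43) = 0.187 SD, or about 0.19.

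**3. Chance imbalance in institution.** With 47 of 94 patients at one institution and 47 per arm, the number of that institution's patients in one arm is hypergeometric. The between-arm difference in share has an SD of 0.104, about 10 percentage points. It is 15 points or more in 9.8% of allocations and 20 points or more in 3.9%. The possible differences are odd multiples of 1/47, so 9/47 (19 points) counts towards the first figure, and 11/47 (23 points) is the first to reach 20. With 28 of 94 at one institution the SD is 0.095. These figures treat institution as unrelated to the two minimisation factors.

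**4. Shift of the estimate in the realised sample.** Shift = imbalance × g.

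| Imbalance | g = 0.3 SD | g = 0.5 SD | Relative to SE 0.187 |
|---|---|---|---|
| 10 points (typical) | 0.03 SD | 0.05 SD | 0.16 to 0.27 |
| 20 points (about 4% of trials) | 0.06 SD | 0.10 SD | 0.32 to 0.54 |

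Against the planned effect, the second row is 0.06/0.53 = 11% to 0.10/0.53 = 19%.

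**5. Residual variance and power without a site term.** A two-level factor with a 50:50 split and effect g adds g²/4 to the residual variance. For g = 0.5 this is 0.75 + 0.0625 = 0.8125, giving a standard error of √(0.8125 × 2/43) = 0.194. For g = 0.3 it is 0.75 + 0.0225 = 0.7725, giving 0.190. A simulation of the planned model (8,000 runs per scenario, 43 per arm, simple randomisation, splits of 50:50 and 70:30) gave, for g = 0.5, power of about 77% without the site term and 79 to 80% with it. For g = 0.3 both were about 79 to 80%.

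**6. Bias and type I error.** In the same simulation the mean estimate without a site term lay at the true value within simulation error, and type I error was 4.8 to 5.3%.

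**7. Price of the site term if site does not matter.** One further degree of freedom takes power at 43 per arm from 80.09% to 80.08%. The required sample size is unchanged.

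**The case against.** The strongest case against is that nothing in the protocol is wrong or contradictory here. Randomisation makes the estimate unbiased, and the standard error already allows for chance imbalance in an omitted covariate. Severity, the main prognostic measure available, is both minimised and adjusted for, and duration is minimised, so case-mix differences acting through severity are largely removed. The 20-point imbalance is a tail event, and even then the shift is only a third to a half of one standard error. All of this stands, and it confines the point to precision.

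Three stronger readings are tempting, and the documents do not support them.

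- *The treatment effect will be biased by site.* It is not: over repeated allocations the unadjusted estimate is unbiased and type I error is about 5%. The shift is conditional on the imbalance that happens to occur.
- *The two institutions deliver different usual care.* The TAU section says "TAU may consist of any treatment the participant or current mental health care specialist sees as necessary". It does not tie TAU to the enrolling institution, and patients may refer themselves, so a site term cannot be assumed to capture differences in usual care.
- *Trainers differ by institution and site adjustment would remove this.* Trainers completed the same two-year programme, use one manual and are videotaped for adherence. Before FU1, any remaining trainer difference acts only in the MBCT arm. That is a site-by-treatment effect, which a main-effect covariate does not remove.

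It is also fair to say that a two-level variable leaves differences among the Pro Persona locations untouched.

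**Conclusion.** The point holds as a modest weakness in a stated design and analysis choice. Institution is omitted from both the minimisation and the models, without comment, although two institutions recruit and run MBCT. The consequence is some lost precision and a possible shift in the realised sample: 0.03 to 0.05 SD at a typical imbalance and 0.06 to 0.10 SD at an imbalance of 20 points, against a standard error of about 0.19 SD. Power falls by about 2 to 3 points if institution shifts FU1 by 0.5 SD, and hardly at all if the shift is 0.3 SD. These sizes rest on an assumed site split and assumed site effects; if institution has no effect beyond baseline IDS-SR, nothing is lost. The case for acting is that the remedy is nearly free, not that the threat is large.

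**What to change.** Prespecify institution (Radboudumc versus Pro Persona) as a fixed covariate in the primary general linear model and in the general linear models for the secondary outcomes, and record this before the outcome data are examined. It applies to all patients, whether or not allocation is complete. The cost is one degree of freedom, with power at about 80% for 43 per arm and no change in sample size.

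Adding institution to the minimisation for patients not yet allocated is optional. It would slightly loosen balance on severity and duration, would need the date of change documented, and in an open-label trial could make the next allocation easier to predict at a site. The covariate alone corrects for a main effect of institution, so the analysis does not depend on that step.
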